#### Secondary outcomes

The following are the secondary outcomes:
i)Absolute difference and relative change in the predicted 10-year ASCVD risk between the intervention and usual care groups at 6 monthsii)Absolute changes in total cholesterol, low-density lipoprotein cholesterol (LDL-C), glycated hemoglobin, and body mass index at 6 monthsiii)Differences between the groups in the change in the proportion of patients reaching treatment goals for systolic blood pressure, total cholesterol, LDL cholesterol, glycated hemoglobin and body mass index at 6 months

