### Participant timeline {13}

Participants will be enrolled and assessed following the Standard Protocol Items: Recommendations for Intervention Trials (SPIRIT) schedule as shown in Table 1

**Table 1 Tab1:** Enrollment and assessment schedule for the study (SPIRIT schedule)

	Study period		
	Enrollment	Allocation	Post-allocation
Time point		0	T1 = 6 months
Enrolment:			
Eligibility screen	X		
Informed consent	X		
Pooled coherent risk equation	X		
Allocation		X	
Intervention:			
Nurse-led lifestyle choice and coaching interventions			
Assessments:			
Baseline variables	- Predicted 10 years ASCVD risk - BMI - Glycated hemoglobin - Systolic blood pressure - Total cholesterol Proportion of patients at target for: - Glycated hemoglobin - Systolic blood pressure - Diastolic blood pressure - Total cholesterol - LDL cholesterol		
Outcome variables			1) Mean change in systolic blood pressure 2) Absolute and relative change in predicted 10-year ASCVD risk 3) Absolute increase in proportion of patients at target for: -Systolic blood pressure -Diastolic blood pressure -Total cholesterol -Glycated hemoglobin -LDL cholesterol

.

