### Sample size {14}

To detect an 8.5-mmHg mean difference in systolic pressure between the intervention and control arms, the sample size was calculated basing on a study by Rudd et al. [31]. The study evaluated the effects of a nurse-led use of algorithm-based prescribing compared to usual care where there was a mean change in systolic blood pressure of 14.2 mmHg (standard deviation (SD) = 17.2) in the intervention arm and 5.7 mmHg (SD = 18.7) in the control arm [31].

To have an 80% power for the trial at a significance level of 0.05, a 2-tailed test assuming an intracluster correlation coefficient (ICC)of 0.035 for continuous clinical outcomes for studies related to cardiovascular disease and management in primary care practices [32] has been used. Given that we shall have 4 fixed clinics (clusters) per arm, the sample size for each arm has been calculated using the formula for a fixed number of equal-sized clusters as described by Hemming et al. [33]. The sample size for each arm will be 174. Assuming a 10% loss to follow-up over the 6 months, the final sample size for each arm will be 193.3 rounded to 194 with each cluster having 49 participants. We recognize that the study may not be powered enough for the secondary outcomes since the sample size has been calculated based on the primary outcome.

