## Data collection and management

### Plans for assessment and collection of outcomes {18a}

After confirming eligibility, trained study nurses will obtain written informed consent and collect data on socio-demographic characteristics and treatment history that will be filled in the data collection forms. Baseline data on systolic blood pressure, total cholesterol, high-density lipoprotein cholesterol, low-density lipoprotein cholesterol, glycated hemoglobin, body mass index, and 10-year predicted ASCVD risk score will be collected and filled in the data collection forms.

Study nurses will measure the blood pressure using an automated OMRON® digital blood pressure machine with an appropriate cuff size placed on the upper arm with the bladder of the cuff centered over the brachial artery. An average of three blood pressure measurements will be obtained.

Weight will be measured to the nearest 0.1 kg with the subject standing motionless on the bathroom weighing scale.

Height will be measured to the nearest 0.1 cm with the subject standing in an erect position against a vertical scale or portable stadiometer and with the head positioned so that the top of the external auditory meatus is in level with the inferior margin of the bony orbit.

Body mass index (BMI) will be calculated as weight in kilogram divided by squared height in meters. Conventional BMI cutoffs will be used to classify the study population into underweight (BMI < 18.5 kg/m^2^), normal BMI (≥ 18.5 < 25 kg/m^2^, overweight BMI > 25 to < 30 kg/m^2^), and obese > 30 kg/m^2^.

Waist and hip circumferences will be measured twice to the nearest centimeter using a non-stretchable measuring tape, and the mean values will be used for subsequent analysis.

Waist circumference (WC) will be measured halfway between the lowest rib and the iliac crest with the subject standing at the end of gentle inspiration. The hip circumference (HC) will be measured at the level of the greater trochanters. The waist to hip ratio (WHR) and the waist to height ratio (WHtr) will be computed for each participant.

After a 12-h fasting, standard calorimetric methods will be used to assay fasting plasma glucose, total cholesterol, triglycerides(TG), and high-density lipoprotein cholesterol (HDL-C). Low-density lipoprotein cholesterol will be calculated using the Friedwald formula when TG levels are equal or less than 4 mmol/l. Low-density lipoprotein cholesterol will be measured directly when TGs are > 4 mmol/l.

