## Statistical methods

### Statistical methods for primary and secondary outcomes {20a}

Participant characteristics will be described using simple descriptive characteristics. We will use the mean and standard deviation to describe normally distributed continuous variables and the median and upper and lower limits of the interquartile range to describe non-normally distributed continuous variables. Normality of continuous variables will be assessed by visual inspection of histograms. Categorical data will be presented in counts and percentages.

Data will be analyzed according to the intention-to-treat (ITT) principle.

The primary outcome of the trial is the mean difference in the change in systolic blood pressure between baseline and 6 months and between the intervention and usual care groups at individual and cluster levels. It will be expressed as the mean systolic blood pressure difference between the groups (with 95% CI).

This value will be measured as the difference between matched diabetes clinics (intervention clinics minus control clinics) in systolic blood pressure (systolic blood pressure in the intervention period minus systolic blood pressure in the baseline period). The hypothesis for this study is that a nurse-led lifestyle choice and coaching intervention reduces systolic blood pressure compared to usual care among type 2 diabetic patients with high ASCVD risk.

In this study, the same individuals will be assessed at baseline and follow-up (cohort design), and analysis of covariance (ANCOVA) will be used to analyze each individual’s outcome at follow-up adjusted for that individual’s outcome at baseline with mixed-effects linear regression or generalized estimating equations to assess changes over time in systolic blood pressure as a continuous variable between clusters [36, 37]. A random intercept representing each cluster will be added to each model to account for the intra-cluster correlation (ICC). We shall adjust the analysis models by the balancing factor urban or peri-urban.

Appropriate analyses will be employed to assess the secondary outcomes between study arms. Since sample size calculation for the trial was based on the primary outcome, the lack of significant differences between the arms may be due to the true lack of differences or due to inadequate power. Therefore, secondary outcome interpretation will be cautiously done.

All analyses will be conducted using the SPSS software version 25.

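### The at-goal secondary outcomes are defined as a difference in change of proportions; 6-month status adjusted for each participant's baseline value would be more precise and uses data already collected

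*Protocol article*

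**What the plan says.** The Protocol article, Outcomes {12}, gives the third secondary outcome as "Differences between the groups in the change in the proportion of patients reaching treatment goals for systolic blood pressure", followed by total cholesterol, LDL cholesterol, glycated hemoglobin and body mass index. Table 1 under Participant timeline {13} has the same idea: "Absolute increase in proportion of patients at target for".

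On predicted 10-year ASCVD risk the two places differ. Outcomes {12} has an absolute difference and a relative change between the groups at 6 months. Table 1 has "Absolute and relative change in predicted 10-year ASCVD risk".

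Statistical methods {20a} applies analysis of covariance, by mixed model or GEE, to "analyze each individual’s outcome at follow-up adjusted for that individual’s outcome at baseline", and names systolic blood pressure as the variable. It adds: "We shall adjust the analysis models by the balancing factor urban or peri-urban". For the rest it says: "Appropriate analyses will be employed to assess the secondary outcomes between study arms".

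The data for adjustment exist. Plans for assessment {18a} lists "Baseline data on systolic blood pressure, total cholesterol, high-density lipoprotein cholesterol, low-density lipoprotein cholesterol, glycated hemoglobin, body mass index, and 10-year predicted ASCVD risk".

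**The concern.** The primary outcome is worded as a change but analysed as a 6-month value adjusted for baseline, which is efficient. The at-goal outcomes are defined by an arm-level quantity, the change in a proportion, with no such adjustment stated. Two things are lost.

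- **Precision.** A change in a yes/no status adds the noise of the baseline status to that of the 6-month status, and it discards how far each participant stood from the goal.
- **Protection against chance imbalance.** With eight clinics the arms can easily start several points apart in the proportion at goal. Because status is only moderately correlated over time, subtracting the whole baseline difference takes off too much: the arm that starts better tends to look worse on change.

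The objectives and hypothesis include ASCVD risk, so it also matters that the article gives that outcome two wordings. The sample-size section already concedes that secondary outcomes may be underpowered, so avoidable loss counts.

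**Working it through.** **Inputs from the article (Sample size {14}).** The target is "To detect an 8.5-mmHg mean difference in systolic pressure between the intervention and control arms". SDs of change are 17.2 and 18.7 mmHg, power 80%, two-sided 0.05, ICC 0.035, 4 clinics per arm, 174 evaluable per arm, 194 after 10% loss.

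**The plan's own figure.**
- Individually randomised n per arm = (17.2² + 18.7²)(1.960 + 0.842)² / 8.5² = 70.1.
- Fixed number of clusters: m = n(1 − ICC)/(4 − n × ICC) = 43.8 per clinic, or 175.1 per arm. With n rounded to 70 it is 174.3.
- 174/0.9 = 193.3, taken to 194.

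The figure reproduces. The point below does not depend on it, but the cluster size and ICC carry over.

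**Assumptions, not in the article.** The baseline to 6-month correlation r of the underlying measurement is 0.3 to 0.8, and the goal lies near the median, so the variance of status is 0.25. For blood pressure the Background reports 56% at or below 140/80 mmHg, which is close to that.

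**At-goal outcomes.** The correlation of status over time is φ = (2/π) arcsin r. Relative to a plain 6-month comparison (= 1), the variance is 2(1 − φ) for the difference in change, and 1 − (2/π)r² for 6-month status adjusted linearly for the continuous baseline value.

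| r | φ | change | adjusted | ratio |
|---|---|---|---|---|
| 0.3 | 0.194 | 1.612 | 0.943 | 1.71 |
| 0.5 | 0.333 | 1.333 | 0.841 | 1.59 |
| 0.6 | 0.410 | 1.181 | 0.771 | 1.53 |
| 0.7 | 0.494 | 1.013 | 0.688 | 1.47 |
| 0.8 | 0.590 | 0.819 | 0.593 | 1.38 |

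Design effect = 1 + (43.5 − 1) × 0.035 = 2.4875. At r = 0.6:
- change: √(2 × 0.25 × 1.181 × 2.4875/174) = 0.092
- adjusted: √(2 × 0.25 × 0.771 × 2.4875/174) = 0.074
- plain 6-month comparison: √(2 × 0.25 × 2.4875/174) = 0.085

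For an illustrative true difference of 20 points, noncentral t on 6 df, power is about 45%, 62% and 51%. If the urban/peri-urban term costs one df, the figures on 5 df are about 42%, 58% and 48%. Up to about r = 0.7, the change in proportions is no more precise than ignoring baseline.

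**Check by simulation.** The formulas apply one design effect throughout, so they take clinic-level and individual-level correlation as equal. A null simulation (8 clinics of 43, ICC 0.035, 56% at goal, 4,000 runs, individual r 0.4 to 0.8, clinic-level r 0.5 to 0.9) relaxed this. The variance ratio of change to adjusted was 1.26 to 1.46.

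**Baseline imbalance.** With 48.5 enrolled per clinic, the design effect is 1 + 47.5 × 0.035 = 2.6625, and the SD of the chance difference in proportion at goal is √(2 × 0.25 × 2.6625/194) = 0.083, about 8 points (about 7 in the simulation). At r = 0.6 a fraction 1 − 0.410 = 0.59 of it, about 5 points, enters the difference in change with reversed sign. In the simulation the correlation of each estimate with the baseline difference was −0.35 to −0.54 for change, +0.38 to +0.73 for the plain 6-month comparison, and −0.13 to +0.28 for the adjusted one.

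**Continuous secondary outcomes.** If raw changes were compared, the variance relative to covariance adjustment would be 2/(1 + r): 1.54 at r = 0.3, 1.33 at 0.5, 1.11 at 0.8. If baseline is a covariate in a linear model, modelling the change or the 6-month value gives the same treatment estimate and nothing is lost.

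**The case against.** The strongest reply is that the article leaves the secondary analyses open and an analysis plan not shown may settle them with baseline adjustment. The primary outcome shows that change wording does not exclude this. That reply holds for the continuous outcomes. It does not fully answer the at-goal outcomes: a model can be left to a later document, but here the outcome itself is defined as a difference in change of proportions.

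A reader might infer more than the text supports:

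- *That predicted risk is compared unadjusted at 6 months.* Nowhere does the article say so, and Table 1 words it as a change. Power figures for an unadjusted comparison would test an analysis that is not stated.
- *That the at-goal comparison carries baseline imbalance into the result.* A change subtracts it and goes too far; carry-over belongs to a plain 6-month comparison.
- *That a difference in change cannot be modelled with clinic effects.* At-goal status at two times with an arm-by-time term, in a GEE or mixed model with identity link, can estimate it.
- *That the relative change in risk is a mean of individual percent changes, with the asymmetry that brings.* The article does not define it.

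It is also fair that a logistic random-intercept model would give a conditional odds ratio, which is harder to read than a difference in proportions. The fix therefore asks for a risk difference.

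**Conclusion.** The point holds for the at-goal outcomes as defined. The difference in change of proportions is less precise than baseline-adjusted 6-month status in every scenario run, by a variance factor of roughly 1.3 to 1.6 (1.26 to 1.46 by simulation; 1.38 to 1.71 by formula for r from 0.8 down to 0.3), and it over-corrects chance imbalance. The size rests on assumed correlations and a goal near the median; the 20-point effect is only an illustration.

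For predicted risk, what stands is narrower: two sections describe the outcome differently, and baseline adjustment is not stated. For the other continuous outcomes the change wording is harmless once baseline is in the model. The primary analysis is untouched, and the article already promises cautious interpretation of secondary results, so this is a worthwhile improvement rather than a threat to the trial.

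**What to change.** In Outcomes {12} and Statistical methods {20a}:

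1. Define each at-goal outcome as 6-month status, compared between arms, adjusted for the participant's own continuous baseline value, with the clinic and urban/peri-urban terms used for the primary outcome. Report a risk difference with its confidence interval.
2. State that predicted ASCVD risk and the other continuous secondary outcomes use the same baseline-adjusted model.
3. Reconcile Outcomes {12} with Table 1 on whether predicted risk is a 6-month difference or a change. If a relative measure is kept, a baseline-adjusted ratio from log risk is one option.

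The cost is a few sentences, with no new data or participants. The one small downside is that a model-based estimate is slightly less simple than raw changes in proportions; those can stay as descriptive results.

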### Participant timeline {13}

Participants will be enrolled and assessed following the Standard Protocol Items: Recommendations for Intervention Trials (SPIRIT) schedule as shown in Table 1

**Table 1 Tab1:** Enrollment and assessment schedule for the study (SPIRIT schedule)

	Study period		
	Enrollment	Allocation	Post-allocation
Time point		0	T1 = 6 months
Enrolment:			
Eligibility screen	X		
Informed consent	X		
Pooled coherent risk equation	X		
Allocation		X	
Intervention:			
Nurse-led lifestyle choice and coaching interventions			
Assessments:			
Baseline variables	- Predicted 10 years ASCVD risk - BMI - Glycated hemoglobin - Systolic blood pressure - Total cholesterol Proportion of patients at target for: - Glycated hemoglobin - Systolic blood pressure - Diastolic blood pressure - Total cholesterol - LDL cholesterol		
Outcome variables			1) Mean change in systolic blood pressure 2) Absolute and relative change in predicted 10-year ASCVD risk 3) Absolute increase in proportion of patients at target for: -Systolic blood pressure -Diastolic blood pressure -Total cholesterol -Glycated hemoglobin -LDL cholesterol

.

### Sample size {14}

To detect an 8.5-mmHg mean difference in systolic pressure between the intervention and control arms, the sample size was calculated basing on a study by Rudd et al. [31]. The study evaluated the effects of a nurse-led use of algorithm-based prescribing compared to usual care where there was a mean change in systolic blood pressure of 14.2 mmHg (standard deviation (SD) = 17.2) in the intervention arm and 5.7 mmHg (SD = 18.7) in the control arm [31].

To have an 80% power for the trial at a significance level of 0.05, a 2-tailed test assuming an intracluster correlation coefficient (ICC)of 0.035 for continuous clinical outcomes for studies related to cardiovascular disease and management in primary care practices [32] has been used. Given that we shall have 4 fixed clinics (clusters) per arm, the sample size for each arm has been calculated using the formula for a fixed number of equal-sized clusters as described by Hemming et al. [33]. The sample size for each arm will be 174. Assuming a 10% loss to follow-up over the 6 months, the final sample size for each arm will be 193.3 rounded to 194 with each cluster having 49 participants. We recognize that the study may not be powered enough for the secondary outcomes since the sample size has been calculated based on the primary outcome.

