**Methods:**

This is a cluster-randomized study comprising two arms (intervention and non-intervention—control arm) with four clusters per arm with 388 diabetic patients with a high predicted 10-year atherosclerotic cardiovascular risk. The study will be implemented in 8 health facilities in Uganda. The intervention arm will employ a nurse-led lifestyle choice and coaching intervention. Within the intervention, nurses will be trained to provide structured health education, protocol-based hypertension management, and general atherosclerotic cardiovascular risk factor management, 24-h phone calls, and 2-monthly text messaging. The control group will be constituted by the usual care. The primary outcome measure is the mean difference in systolic blood pressure between the intervention and usual care groups after 6 months. The study is designed to have an 80% statistical power to detect an 8.5-mmHg mean reduction in systolic blood pressure from baseline to 6 months. The unit of analysis for the primary outcome is the individual participants. To monitor the effect of within-cluster correlation, generalized estimating equations will be used to assess the changes over time in systolic blood pressure as a continuous variable.

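### The stated 80% power for 8.5 mmHg rests on a normal approximation that ignores having only eight randomised clinics; on the same inputs a t-based calculation gives about 61–65% before any gain from baseline adjustment

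*Protocol article*

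**What the plan says.** The Sample size section {14} sets the target as follows: "To detect an 8.5-mmHg mean difference in systolic pressure between the intervention and control arms". The figure comes from a cited trial with a "mean change in systolic blood pressure of 14.2 mmHg (standard deviation (SD) = 17.2) in the intervention arm"; its usual-care patients fell by 5.7 mmHg with an SD of 18.7, so 8.5 = 14.2 − 5.7. The error rates are given in one sentence: "To have an 80% power for the trial at a significance level of 0.05, a 2-tailed test". The ICC is 0.035 and there are four clinics per arm. On method, "the sample size for each arm has been calculated using the formula for a fixed number of equal-sized clusters", and the result is "The sample size for each arm will be 174", raised to 194 for 10% loss to follow-up. The section mentions no degrees of freedom and no small-sample correction.

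The Statistical methods section {20a} plans an ANCOVA of follow-up systolic pressure on baseline, by mixed model or GEE, with a random intercept for clinic. It adds: "We shall adjust the analysis models by the balancing factor urban or peri-urban".

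The Methods paragraph of the abstract says the study is "designed to have an 80% statistical power to detect an 8.5-mmHg mean reduction in systolic blood pressure from baseline to 6 months".

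**The concern.** Clinics are randomised, and there are eight. The arm contrast is therefore judged against variation between clinics, which is estimated on 8 − 2 = 6 degrees of freedom, or 5 once a clinic-level covariate is in the model. The two-sided 5% critical value is then 2.447 or 2.571, not 1.960. A calculation that uses 1.960 promises a power and a significance level that the design does not deliver together on those inputs.

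The stake is how a null primary result is read. The protocol's warnings about limited power cover the secondary outcomes only, so a reader would take the primary comparison as having 80% power for 8.5 mmHg without condition. The Discussion says the findings should feed national guidelines.

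The abstract adds a separate, smaller problem. A fall from baseline within an arm and a between-arm difference in change are different quantities; in the cited trial they were 14.2 and 8.5 mmHg.

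**Working it through.** **Inputs** (Sample size {14}): difference 8.5 mmHg; SDs of change 17.2 and 18.7; ICC 0.035; k = 4 clinics per arm; 174 evaluable per arm, so m = 174/4 = 43.5 per clinic. The mean variance is (17.2² + 18.7²)/2 = 322.8, SD 17.97.

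**1. Reproducing 174.** The individually randomised size per arm is

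n_I = (1.960 + 0.842)² × (17.2² + 18.7²)/8.5² = 70.1.

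The formula for a fixed number of clusters gives m = n_I(1 − ICC)/(k − n_I × ICC). With n_I = 70, m = 70 × 0.965/(4 − 2.45) = 43.6 per clinic, or 174.3 per arm. Unrounded, it is 175.1. Dropout: 174/0.9 = 193.3, rounded up to 194. The arithmetic is sound.

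The protocol does not name its quantiles, but the result identifies them. On 6 df, 80% power would need about 215 evaluable patients per clinic (860 per arm), so 174 cannot contain a small-cluster allowance.

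**2. Standard error.** SE = √[2 × 322.8 × (0.035 + 0.965/43.5)/4] = 3.04 mmHg. The noncentrality is 8.5/3.04 = 2.80. Power with a 1.960 cut-off is 79.9%, which is the stated 80%.

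**3. Same SE, t reference distribution** (noncentral t):

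| df | critical value | power at 8.5 mmHg | difference detectable with 80% power |
|---|---|---|---|
| 6 | 2.447 | 64.8% | 10.2 mmHg |
| 5 (urban/peri-urban term) | 2.571 | 61.4% | 10.7 mmHg |

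If all 194 per arm are retained (m = 48.5), power is 66.5% and 63.1%. If the 1.960 cut-off were kept, the true type I error would be about 9.8% (6 df) or 10.7% (5 df).

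**4. Baseline adjustment and ICC.** The SDs above are for change scores, but the plan is ANCOVA. Assume equal variances at the two times, a baseline–follow-up correlation r and the same ICC. ANCOVA then multiplies the variance of the change-score contrast by (1 + r)/2, so the noncentrality is divided by √[(1 + r)/2]. At r = 0.5 this is 2.80/√0.75 = 3.23. The protocol gives no r, and the ICC values 0.02 and 0.05 are also assumptions. Power (6 df / 5 df) for m = 43.5:

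| ICC | change score | ANCOVA r = 0.7 | r = 0.5 | r = 0.3 |
|---|---|---|---|---|
| 0.02 | 77% / 74% | 83% / 80% | 87% / 85% | 91% / 89% |
| 0.035 | 65% / 61% | 72% / 68% | 77% / 73% | 82% / 79% |
| 0.05 | 55% / 52% | 62% / 59% | 67% / 64% | 73% / 70% |

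**The case against.** The strongest reply is that 61–65% is not the power of the planned analysis. It belongs to an unadjusted comparison of changes, whereas the protocol commits to ANCOVA. At r = 0.3 the gap closes almost entirely, and at ICC 0.02 the planned analysis reaches 80% or more across the range of r shown. The ICC is a general value for continuous clinical outcomes and may not suit baseline-adjusted pressure. The 5-df figures also charge the urban/peri-urban term one degree of freedom without crediting any between-clinic variance it may explain.

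This stands, and it limits the point. A reader might infer that the trial has only 61–65% power, that its chance of missing 8.5 mmHg is 35–39%, or that no test holding 5% could reach 80%. The documents support none of these, because the power of the planned ANCOVA depends on an r they do not give. Nor do they settle on a four-pair analysis with 3 df: one sentence speaks of matched clinics, but the model described has a clinic random intercept and a stratum term.

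Two further replies carry less weight. The choice of degrees of freedom for the final test may well be in the analysis plan, but the power figure and its inputs are stated here. And a named formula was indeed applied correctly; what fails is its large-sample approximation with four clinics per arm.

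On the abstract, the preceding sentence does define the outcome as a between-group difference. The power sentence is therefore a wording error, not a second target.

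**Conclusion.** The concern holds in a limited form. On the basis the protocol gives, 80% power and a two-sided 5% level do not hold together: change-score power is about 65% (6 df) or 61% (5 df), and 80% power corresponds to 10.2 or 10.7 mmHg. The sample-size section takes no credit for baseline adjustment. If it did, at ICC 0.035 power would lie at about 72–82% (6 df) or 68–79% (5 df) for r from 0.7 down to 0.3, assuming the (1 + r)/2 variance factor and an unchanged ICC. The 80% may therefore be nearly right for the planned analysis under favourable values of r and ICC, but nothing in the protocol states or justifies those values. All figures assume equal cluster sizes and a stratum term that explains no between-clinic variance. The abstract's description of 8.5 mmHg is wrong whichever figure applies.

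**What to change.** Keep the 8 clinics and 388 patients.

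- In Sample size {14} and the abstract, replace the unqualified 80% with power from a t reference distribution on 5–6 df. Suggested wording: with four clinics per arm, 174 evaluable patients per arm and ICC 0.035, power for an 8.5 mmHg between-arm difference in change is about 61–65% for an unadjusted change-score comparison (80% power corresponds to about 10.2–10.7 mmHg); for the planned baseline-adjusted analysis it is about 68–82% for an assumed baseline–follow-up correlation of 0.7 to 0.3.
- Give the source or rationale for the range of r, and show the sensitivity to the ICC in both directions, for example 0.02 to 0.05.
- In the abstract, describe 8.5 mmHg as the between-arm difference in change from baseline to 6 months.

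The cost is wording only. The downside is that the stated power becomes less favourable and conditional on assumptions the reader can see.
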